## Abstract

**Introduction:**

Myalgic encephalomyelitis/chronic fatigue syndrome (ME/CFS), is a debilitating illness affecting up to 24 million people worldwide but concerningly there is no known mechanism for ME/CFS and no objective test for diagnosis. A series of our neuroimaging findings in ME/CFS, including functional MRI (fMRI) signal characteristics and structural changes in brain regions particularly sensitive to hypoxia, has informed the hypothesis that abnormal neurovascular coupling (NVC) may be the neurobiological origin of ME/CFS. NVC is a critical process for normal brain function, in which glutamate from an active neuron stimulates Ca^2+^ influx in adjacent neurons and astrocytes. In turn, increased Ca^2+^ concentrations in both astrocytes and neurons trigger the synthesis of vascular dilator factors to increase local blood flow assuring activated neurons are supplied with their energy needs.

This study investigates NVC using multimodal MRIs: (1) hemodynamic response function (HRF) that represents regional brain blood flow changes in response to neural activities and will be modeled from a cognitive task fMRI; (2) respiration response function (RRF) represents autoregulation of regional blood flow due to carbon dioxide and will be modeled from breath-holding fMRI; (3) neural activity associated glutamate changes will be modeled from a cognitive task functional magnetic resonance spectroscopy. We also aim to develop a neuromarker for ME/CFS diagnosis by integrating the multimodal MRIs with a deep machine learning framework.

**Methods and analysis:**

This cross-sectional study will recruit 288 participants (91 ME/CFS, 61 individuals with chronic fatigue, 91 healthy controls with sedentary lifestyles, 45 fibromyalgia). The ME/CFS will be diagnosed by consensus diagnosis made by two clinicians using the Canadian Consensus Criteria 2003. Symptoms, vital signs, and activity measures will be collected alongside multimodal MRI.

The HRF, RRF, and glutamate changes will be compared among four groups using one-way analysis of covariance (ANCOVA). Equivalent non-parametric methods will be used for measures that do not exhibit a normal distribution. The activity measure, body mass index, sex, age, depression, and anxiety will be included as covariates for all statistical analyses with the false discovery rate used to correct for multiple comparisons.

The data will be randomly divided into a training (*N* = 188) and a validation (*N* = 100) group. Each MRI measure will be entered as input for a least absolute shrinkage and selection operator—regularized principal components regression to generate a brain pattern of distributed clusters that predict disease severity. The identified brain pattern will be integrated using multimodal deep Boltzmann machines as a neuromarker for predicting ME/CFS fatigue conditions. The receiver operating characteristic curve of the identified neuromarker will be determined using data from the validation group.

**Ethics and study registry:**

This study was reviewed and approved by University of the Sunshine Coast University Ethics committee (A191288) and has been registered with The Australian New Zealand Clinical Trials Registry (ACTRN12622001095752).

**Dissemination of results:**

The results will be disseminated through peer reviewed scientific manuscripts and conferences and to patients through social media and active engagement with ME/CFS associations.

## Introduction

Myalgic encephalomyelitis/chronic fatigue syndrome (ME/CFS) is a serious, long-term illness for which the underlying disease process remains unknown, and no objective diagnostic test exists. The disease is characterized by profound fatigue for more than 6 months, cognitive and motor dysfunction, unrefreshing sleep, and/or orthostatic intolerance (1). There are 17 to 24 million people affected by ME/CFS, with 25% of them housebound (2). In addition to enduring the disease itself and its economic burden, 80% of ME/CFS patients struggle to get a diagnosis and are often left depressed by the lack of a diagnostic certainty and medical understanding of the disease processes. Although the etiology of ME/CFS remains unresolved, the well-documented autonomic dysfunction, sleep disturbance, cognitive impairments, altered sensory and pain perception, and reduced motor speed suggest that abnormal brain function plays a crucial role in the underlying disease process of ME/CFS (3). As such, ME/CFS has been classified as a neurological disease (ICD code 10 G93.3) by the WHO.

Additional brain area recruitment associated with cognitive tasks during task fMRI is one of the most frequently observed differences between patients with ME/CFS and controls (4). The task fMRI signal was based on neurovascular coupling (NVC), the dynamic regulation of blood flow induced by neural activity. NVC is a critical process for normal brain function, in which glutamate from an active neuron stimulates Ca^2+^ influx in adjacent neurons and astrocytes. In turn, increased Ca^2+^ concentrations in both astrocytes and neurons trigger the synthesis of vascular dilation factors to increase local blood flow, ensuring activated neurons are supplied with their energy needs (5, 6). Previous genetic and electrophysiological studies showed that transient receptor potential melastatin subfamily 3 (TRPM3) activity and Ca^2+^ mobilization were reduced in ME/CFS (7–9). Reduced Ca^2+^ mobilization may delay NVC and result in the less responsive fMRI signals (i.e., coupled less tightly with tasks with lower sample entropies) that were observed in our previous neuroimaging study (10). The delayed NVC ensues subtle brain changes, culminating in chronic brain injury and associated cognitive impairment (5), presenting as structural changes in brain regions (11–16) susceptible to hypoxia. Moreover, we postulate that a higher level of glutamate is released because of delayed NVC in ME/CFS patients and results in additional brain area recruitment during tasks (4, 10). Excess glutamate may cause excitotoxicity, which is consistent with increased expression of the vasoactive intestinal peptide receptor 2 observed in ME/CFS (17). The intestinal peptide receptor 2 is a neuroprotective agent against excitotoxicity and is released in response to high levels of glutamate (18). Thus, we hypothesize that delayed NVC may explain hypoxia-related brain structural changes and excess glutamate in ME/CFS, which further impairs the brain because of excitotoxicity.

Our previous studies have described brain differences in ME/CFS, related to the brain structure, functional networks (11–13, 15, 16, 19), and BOLD signal changes (10, 20). Although none of these differences alone can differentiate ME/CFS from normal and other disorders, they suggested that a unique brain signature for ME/CFS may be identifiable. Thus, we will also use the least absolute shrinkage and selection operator—regularized principal components regression (LASSO-PCR) (21), to identify brain signatures that contribute to reliable prediction. Then multimodal deep Boltzmann machine (DBM) (22) will be used to integrate multimodal signatures with cross-modality information to develop a neuromarker for objective diagnosis of ME/CFS.

The present paper summarizes the research protocol that addresses the aforementioned aims. We report the analysis plans here to reduce the file-drawer effect and improve the study reproducibility, which is currently solicited in translational research (23) and more urgently required in ME/CFS because of the controversy associated with this ill-defined disease (24).

## Methods and analysis

### The study design

The multimodal MRIs of ME/CFS is a cross-sectional study that commenced in January 2020 and will be completed in December 2024. Participants who express an interest will be screened for eligibility according to inclusion/exclusion criteria. Symptom scores, activity levels, MRIs (detailed below) will be collected after receiving written consent from eligible participants (Figure 1).

**Figure 1 F1:**
[figure not shown]
Flowchart for data collection.

### The primary outcomes

#### Aim 1

To establish *group* differences in Hemodynamic Response Function (HRF) and its relationship to fatigue severity in ME/CFS patients using functional MRI (fMRI).

#### Aim 2

To establish *group* differences in dynamic glutamate activity during cognitive tasks and its relationship to fatigue severity in ME/CFS patients using functional magnetic resonance spectroscopy (fMRS).

#### Aim 3

To develop a neuromarker for ME/CFS diagnosis. The neuromarker will be relevant brain features integrated from multiple MRI modalities using a deep learning framework and validated using independent data.

### The secondary outcomes

i To compare brain structural and functional differences and associations with symptoms among ME/CFS, fibromyalgia, chronic fatigue, and healthy controls (HCs).ii To establish *group* differences in high-frequency heart rate variability and associated fMRI signal changes in ME/CFS.iii To establish *group* objective sleep quality differences and associated brain structure and function differences in ME/CFS.iv To establish *group* differences in sleep measures and changes low- and high-frequency heart rate variability during awake and sleep before and after MRI scanning.v To establish the repeatability of fMRS measures.

### The recruitment and selection of the sample population

We will recruit 288 adult participants (18–65 years old), including 91 patients with ME/CFS, 61 individuals with chronic fatigue, 91 HCs with sedentary lifestyles, and 45 patients with fibromyalgia. The risk of an ill-defined ME/CFS patient cohort will be mitigated by employing a consensus diagnosis of ME/CFS from two clinicians ([name] and [name], both have over 10 years of experience in ME/CFS) and using the Canadian Consensus Criteria (CCC) 2003 (1). This study will also include groups of fibromyalgia, a frequent co-morbidity of ME/CFS. The American College of Rheumatology (ACR) 2016 fibromyalgia criteria (25) will be used for screening and followed by clinic diagnosis by a rheumatologist ([name]). The chronic fatigue is defined as self-identified ME/CFS but not confirmed by the two clinicians (i.e., present with other conditions or lack core ME/CFS symptoms) or with other disorders (not ME/CFS or fibromyalgia) that fatigue is a significant symptom. These two groups are included to ensure specificity of the identified neuromarker. Patients with ME/CFS have reduced daily activity because of their illness. However, a sedentary lifestyle itself may affect brain structure and function. Therefore, there is a risk of identifying brain structural or functional differences from ME/CFS sequelae, rather than from the illness per se. This study will mitigate against this problem by selecting HCs with sedentary lifestyles. A sedentary lifestyle will be defined as spending <60 min in moderate or high-intensity activity (i.e., exercise) per week (26). Furthermore, activity level will be monitored by the Actigraph GT3X-BT device (ActiGraph LLC., United States) for 14 days. The recorded activity level will be included as covariates for all statistical analyses but will not change participants' eligibility.

The inclusion criteria include adult individuals who express an interest, meet each group definition, and are confirmed by clinicians.

The exclusion criteria include individuals (1) out of the age range, (2) pregnant, (3) with severe intellectual or mental impairment preventing them from fully understanding the study to give consent, (4) with mental disorders including post-traumatic stress disorder, obsessive compulsive disorder, schizophrenia, and bipolar disorder, (5) with a known other neurological disorder, (6) who cannot read and communicate in English, (7) recruited by supervising relationship or where a conflict of interest exists, (8) with alcohol or substance related disorder, (9) with BMI >35, (10) smoking (including marijuana or substance usage), (11) with diabetes, hypertension, or uncontrolled hyperlipidaemia, (12) currently on medication acting on the brain, (13) with a clinical diagnosis of hemochromatosis, (14) with a double copy of the Haemochromatosis gene, (15) who experienced migraines more than six times a year before the onset of their symptoms. A researcher will check the exclusion criteria at the screening stage. After the screening process, a differential diagnostic list will be completed by each participant and discussed with two clinicians for diagnosis of ME/CFS during clinical interviews.

Additional exclusion criteria for HCs include individuals (1) with a chronic disease, i.e., a condition that last 1 year or more and require ongoing medical attention or limit activities of daily living or both, including heart disease, stroke, lung cancer, colorectal cancer, depression, type 2 diabetes, arthritis, osteoporosis, asthma, chronic obstructive pulmonary disease, chronic kidney disease, and (2) who experience migraines more than six times a year, and (3) who do more than 60 min in moderate or high-intensity activity per week.

### Data collections

#### Symptom questionnaires

After informed consent has been obtained, the following assessments will be undertaken: (1) symptom information relevant to establishing CCC ME/CFS classification (1); (2) the 36-item Short-Form Health Survey; (c) Hospital Anxiety and Depression Scale questionnaire; (d) the Bell disability score; (e) The Assessment of Quality of Life questionnaire; (g) the Pittsburgh sleep quality index questionnaire.

#### Clinical interviews

Two clinicians ([name] and [name]) will perform a remote interview independently with patients. Prior to the clinical interviews, height, weight, BMI, blood pressure, pulse rate, oxygen saturation, weighted standing time for evaluation of postural orthostatic tachycardia syndrome (POTS) (27), and the Beighton scores (a measure of generalized joint hypermobility) (28) for each participant will be collected and shared with the clinician. The clinician requested the POTS and the Beighton scores to assist diagnosis of ME/CFS. None of the POTS or the Beighton scores alone differentiates ME/CFS but will be used with other measures by clinicians.

#### Actigraphy

Participants will be given a GT3X-BT device with a heart rate monitor to wear 7 days before the MRI. The heart rate monitor is to be worn for 24 h. After the MRI scan, participants will be given another GT3X-BT device to wear for 7 days with a 24-h heart rate monitor to be worn on the next morning of the MRI scan. We will collect actigraphy data before and after the MRI scanning (i) to obtain a robust estimations of activity levels, sleep qualities, and heart rate variabilities and (ii) to investigate sleep quality and heart rate variability changes after a moderate exertion (MRI scanning) in ME/CFS.

#### Multimodal MRI

Brain images are acquired using a 3T MRI scanner with a 64-channel head coil (Skyra, Siemens) at the Thompson Institute (TI), University of the Sunshine Coast (UniSC). A fatigue state questionnaire that measures current fatigue levels (29) will be completed before and after the MRI for each participant. The MRIs will include:

I Structural MRI (sMRI) using a T1-weighted magnetization prepared rapid gradient-echo sequence (MPRAGE): 208 slices, dimension 256 × 256, voxel size 1 mm × 1 mm × 1 mm, TR/TE 2,200/1.71 ms, flip angle 7°.II A set of resting-state fMRI (rsfMRI, 192 volumes) using a multiband EPI sequence: 108 slices, dimension 126 × 126, multiband = 4, dimension 138 × 138, 1.6 mm^3^ isotropic voxel, TR/TE 2,500/42 ms, flip angle 75°. Participant will be instructed to keep their eyes open with fixation of a cross for 8 min acquisition. Heart rate will be recorded simultaneously using pulse oximetry from the MRI scanner.III A set of task fMRI (tfMRI, 800 volumes) using a multiband EPI sequence (60 slices, multiband = 8, dimension 74 × 74, 3 mm^3^ isotropic voxels, TR/TE 800/33 ms, flip angle 65°) while participants perform a symbol digit modalities test (SDMT), which is widely used for cognitive evaluation of information processing speed. A semi-random design, which simultaneously achieves maximum estimation efficiency and detection power, (30) was used (Figure 2). The paradigm is incorporated into the scanner's fMRI sequence for general linear modeling of BOLD signal changes associated with tasks. Brain regions with BOLD signal changes associated tasks are used for voxel location of functional magnetic resonance spectroscopy (fMRS).IV A set of breath-holding fMRI (BH fMRI, 324 volumes) will be acquired using the same pulse sequence and parameters as tfMRI above. Participants perform 6 BH tasks; each BH task consists of 14.4 s (18 fMRI volumes) natural breath, 3 paced breathing (4.8 s each with 2.4 s breath in and out, respectively) of 14.4 s and a 14.4 s end-expiration breath-hold.V A set of fMRS using the HERMES (Hadamard Encoding and Reconstruction of MEGA-Edited Spectroscopy) acquisition method with TR/TE = 2,000/23 ms. The task paradigm is the same as the tfMRI paradigm (Figure 2), during which 16 and 5 measurements (averaged from 8 volumes per measurement) are collected for task and resting block, respectively. A single cuboid voxel, 20 mm (superior-inferior), 27 mm (anterior-posterior), and 12 mm (left-right), covering the left dorsal prefrontal cortex, is adjusted according to individual BOLD activation maps (Figure 3).VI A set of diffusion tensor images (DTI) using a multiband EPI sequence (72 slices, multiband factor 3, dimension = 114 × 114, voxel size 2 × 2 × 2 mm^3^, TR/TE = 4,500/123 ms; free diffusion mode, 96 diffusion directions, bipolar diffusion scheme with two diffusion weighting of b = 0 and b = 2,500, phase encoding direction = anterior to posterior). Six volumes of b = 0 with phase encoding direction in posterior to anterior are also collected for the eddy current correction.VII A final set of rsfMRI will be collected using the same setting as II.

**Figure 2 F2:**
[figure not shown]
The semi-random design of task fMRI paradigm. The semi-random task paradigm (maximizing both estimation efficiency and detection power) includes two alternative tasks and resting conditions blocks (640 sec). Each task block has 30 symbol digit modalities task (SDMT) trials. Each trial takes 5s with a random inter-trial interval ranging from 1–5s (average of 3s). The SMDT requires participants to determine if the lower symbol digit pair agrees with upper symbol-digit references and respond with yes and no keys. Participants keep their eyes open with a cross fixation during the inter-trial intervals and the resting blocks.

**Figure 3 F3:**
[figure not shown]
Real-time task fMRI guided functional magnetic resonance spectroscopy (fMRS). A general linear model determined BOLD signal changes associated with the symbol digit modalities test implemented on the MRI scanner with a threshold of uncorrected *P* < 0.001. A cuboid voxel covering the left dorsal prefrontal cortex (20 mm from superior to inferior, 27 mm from anterior to posterior, and 12 mm from left to right) is adjusted according to BOLD activation maps, **(A)** coronal and **(B)** sagittal views, and **(C)** T1-weighted anatomic images to cover left dorsal prefrontal cortex. **(D)** An example of a measurement averaged from 8 volumes from another participant shows the exact anatomical location and the acceptable signal-to-noise ratio for estimating the glutamate level.

### Data analysis plan

The measured variables will firstly be tested for normal distribution. Equivalent non-parametric methods will be used if any variable does not exhibit a normal distribution. The activity measure, body mass index, age, depression, and anxiety will be included as covariates for all statistical analyses. The false discovery rate (FDR) will be used to correct for multiple comparisons.

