#### Group difference in hemodynamic response function (HRF) (Aim 1)

The HRF features will be compared using one-way analysis of covariance (ANCOVA) among the four groups. The respiration response function (RRF) will be modeled in the breath-holding tfMRI data. This will enable us to disentangle non-neuronally-induced cerebrovascular reactivity from the neurovascular coupling effects. The RRF will be summarized similarly to the HRF by amplitude (*H*), time to peak (*T*), onset (*O*), and width (*W*). The RRF features at the same brain location will be used as a covariate in the HRF ANCOVA analysis to exclude confounding cerebrovascular reactivity (e.g., RRF-*H* as a covariate for HRF-*H* comparison, etc.,). Group differences in each RRF feature will also be tested using ANCOVA among the four groups. The bivariate correlation will be tested between the HRF/RRF features and the health scores. Additionally, the extent to which these correlated features explain variance in the health scores after accounting for all other variables will be evaluated using hierarchical regression.

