### Controlling confounding factors

ME/CFS is an illness currently defined by consensus criteria and questionnaires completed by patients. Thus, there is a risk of an ill-defined ME/CFS patient cohort. The proposed study will mitigate this problem by following CCC ME/CFS criteria and diagnosis agreed by two experienced clinicians ([name] and [name]).

Patients with ME/CFS or fibromyalgia may have ongoing medications, which is logistically unavoidable for the study. We mitigate this risk by following steps. (1) Individuals using marijuana or substance were excluded because their known alteration of brain structure and function. (2) Each medication will be determined individually by agreement of investigators ([name], [name] and [name]) on whether it affects the NVC. We include individuals on medication that does not affect the NVC. (3) Two clinicians ([name] and [name]) will assess individuals on medication affecting the NVC to determine if it is safe to stop medication for 3 weeks. Individuals considered safe to stop medication will further seek professional opinions from their caring physicians and then stop medication 2 weeks before and 1 week after MRI. We will exclude individuals who are at risk to stop medication affecting the NVC.

Both ME/CFS and fibromyalgia predominantly affect females (39). Thus, we may recruit more females than males. Indeed, our current sample includes 82% female and 18% male in all groups, including HCs. This unequal sex ratio risk cannot be avoided because of diseases' inherent features. We will include sex as a covariate in all statistical analyses.

This project started when the severe acute respiratory syndrome coronavirus 2 (SARS-CoV-2) occurred before the long Covid (post-acute sequelae of SARS-CoV-2 infection) was recognized. We decided to keep the study protocol and follow the CCC ME/CFS criteria while considering SAR-CoV-2 as an infection similar to other infections that occurred before the manifestation of ME/CFS.

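### A normality pre-test on the measured variables picks between ANCOVA and an unnamed non-parametric method, mixing tests across outcomes and leaving it open whether covariate adjustment survives the switch

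*Protocol article*

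**What the plan says.** The opening of the Data analysis plan sets a two-step rule. First, "The measured variables will firstly be tested for normal distribution". Then, "Equivalent non-parametric methods will be used if any variable does not exhibit a normal distribution". The abstract applies the same rule measure by measure: "Equivalent non-parametric methods will be used for measures that do not exhibit a normal distribution". Neither place mentions residuals or names the non-parametric method.

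The next sentence of the Data analysis plan reads "The activity measure, body mass index, age, depression, and anxiety will be included as covariates for all statistical analyses". The Discussion (Controlling confounding factors) adds "We will include sex as a covariate in all statistical analyses". False-discovery-rate control is then promised for multiple comparisons.

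For Aim 1, "The HRF features will be compared using one-way analysis of covariance (ANCOVA) among the four groups". That analysis carries one further covariate: "The RRF features at the same brain location will be used as a covariate in the HRF ANCOVA analysis to exclude confounding cerebrovascular reactivity". Aim 2 uses ANCOVA across the same four groups for the glutamate response.

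**The concern.** Four things are wrong with the rule as stated.

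- **It tests the wrong object.** ANCOVA assumes roughly normal errors given group and covariates. It does not require the measured variables to be normal.
- **It lets a significance test choose the analysis.** With about 250 participants, a normality test detects departures that do not disturb the F test. The method is then changed where no change is needed.
- **It can mix methods within one family.** HRF and RRF are each summarised by amplitude, time to peak, onset and width, at regional level. Under the rule, one feature or region could be compared on adjusted means and its neighbour on ranks. The p-values would enter one false-discovery-rate procedure while answering different questions.
- **It is not reconciled with the covariate promise.** The familiar non-parametric counterpart of a one-way comparison, Kruskal-Wallis, takes no covariates. If an analyst used it, adjustment for depression, anxiety, activity, body mass index, age and sex would go. So would the matching RRF covariate, on which Aim 1 relies to separate neurovascular coupling from vascular reactivity.

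Losing adjustment would matter because group differences on the covariates are foreseeable. The recruitment section says "Patients with ME/CFS have reduced daily activity because of their illness", and depression as a chronic disease excludes healthy controls only.

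**Working it through.** The plan gives no figure for this point, so its sample size is used as the starting input and the operating characteristics are simulated.

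**Inputs from the document.** Planned groups are 91 ME/CFS, 61 chronic fatigue, 91 controls and 45 fibromyalgia, 288 in total. The power analysis assumes that 87% of data are valid: 251/0.87 = 288.5, which agrees with 288. Group by group, 0.87 × 91 = 79.2, 0.87 × 61 = 53.1 and 0.87 × 45 = 39.2. The simulations therefore use 79/53/79/39, 250 in all.

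**Assumptions not in the document.** There is one covariate x with within-group SD 1. It is shifted by 0, 0.5 or 1.0 SD in ME/CFS, by 80% of that in chronic fatigue and fibromyalgia, and by 0 in controls. The outcome is y = r·x + √(1 − r²)·e, with r = 0.3 or 0.5 and no group effect after adjustment. The error e is standard normal or a standardised gamma with shape 2 (skewness 2/√2 = 1.41). The pre-test is Shapiro-Wilk at 0.05 on the pooled raw outcome. The two-stage rule uses Kruskal-Wallis after a rejection and ANCOVA otherwise. Each row has 1,500 runs, so the Monte Carlo standard error at 5% is √(0.05 × 0.95/1500) = 0.6 percentage points.

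**Step 1. How often the rule switches, and the false-positive rate at nominal 5%.**

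| Error | Shift | r | Switch | ANCOVA | Two-stage with Kruskal-Wallis | Rank ANCOVA |
|---|---|---|---|---|---|---|
| skewed | 0 | 0.3 | 100% | 4.5% | 5.5% | 5.0% |
| skewed | 0.5 | 0.3 | 100% | 5.1% | 14.1% | 5.2% |
| skewed | 0.5 | 0.5 | 99% | 4.3% | 28.5% | 4.7% |
| skewed | 1.0 | 0.3 | 100% | 4.7% | 45.0% | 5.0% |
| skewed | 1.0 | 0.5 | 99% | 3.7% | 83.7% | 3.9% |
| normal | 0.5 | 0.3 | 5% | 5.4% | 5.5% | 6.1% |
| normal | 1.0 | 0.5 | 5% | 4.7% | 7.8% | 5.1% |

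Plain ANCOVA holds its level on the very data that trigger the switch. The inflation comes from the loss of the covariate: with no covariate shift, the two-stage rule sits at 5.5%.

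**Step 2. Mild skew.** A gamma with shape 20 has skewness 2/√20 = 0.45. Shapiro-Wilk rejected such a variable in 73% of samples. It rejected an outcome with that error plus a covariate contribution (slopes 0.1 to 0.3) in 56% to 70%. With covariate shifts of +1.0/+0.9/0/+0.9 SD and slopes 0.1, 0.2 and 0.3, the two-stage rule with Kruskal-Wallis gave 7%, 14% and 22% false positives. ANCOVA and rank ANCOVA both stayed at 4% to 6%.

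**Step 3. Would moving the test to residuals cure it?** No. In every skewed row of the table, Shapiro-Wilk on the ANCOVA residuals rejected in 100% of runs, against 99% to 100% on the raw outcome. Changing the object of the test corrects the principle but not the switching. The pre-test itself has to go.

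**The case against.** The strongest reply is that the document never says adjustment is dropped. The sentence after the switch rule keeps covariates in all analyses, and the equivalent of ANCOVA can fairly be read as a covariate-adjusted rank or permutation method. Kruskal-Wallis appears nowhere. This stands. A reader might infer that the rule will remove the adjustment, but the text supports only that it could, because no method is named. The 14% to 84% rates belong to an unadjusted fallback alone.

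Three further inferences do not hold.

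- *Adjustment is lost specifically where groups differ on covariates.* The main covariates are participant-level and are equally imbalanced in every analysis. What triggers the switch is skewness of the outcome: with normal errors it fires in about 5% of runs at every covariate shift.
- *Pooling four groups makes the raw variable materially non-normal.* With normal errors and group effects of f = 0.25 (the plan's own target) or 0.40, Shapiro-Wilk on the pooled variable rejected in 4.8% to 5.4% of runs, against 4.7% to 5.0% with no effect.
- *The bounded anxiety and depression scores force the switch for the imaging outcomes.* Those scores enter the group comparisons as covariates, and the abstract applies the rule to the measures being compared.

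It is also fair that the sedentary-control criterion is meant to narrow the activity gap, and that a condensed article may leave the name of a procedure to the analysis plan. The second point excuses the missing name. It does not excuse the rule, which is stated, refers to measured variables, and makes the method depend on a significance test.

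**Conclusion.** The point holds as a defect in a stated decision rule. It does not show that the trial will run unadjusted tests. Firm conclusions, on the planned group sizes: the rule tests the wrong object, it often fires on mild skew (56% to 73% of samples at skewness 0.45), and it brings no type I benefit, since ANCOVA stays at about 4% to 6%. It can also combine different estimands within one false-discovery-rate family.

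The conditional conclusion is that, if the unnamed fallback were Kruskal-Wallis, false positives for strongly skewed outcomes would be 14% to 45% at r = 0.3 and 29% to 84% at r = 0.5, for covariate shifts of 0.5 to 1 SD. With a covariate-adjusted rank method there is no inflation. The shifts, correlations and error shapes are assumptions, and the simulation uses a single covariate. The document gives no variances or means for these measures. This should be changed, because the change is cheap and removes an avoidable ambiguity from the primary comparisons.

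**What to change.** Delete the pre-test on measured variables from the Data analysis plan and the abstract. In its place, state that every outcome in Aims 1 and 2 is analysed with the same covariate-adjusted linear model, with the full covariate list including sex and, for each HRF feature, the matching RRF feature. Choose one form of inference in advance for all outcomes: heteroscedasticity-robust (HC3) or Freedman-Lane permutation p-values. Inspect residuals as a diagnostic that is reported but does not select the method. Name a rank-based ANCOVA that keeps all covariates as a pre-stated sensitivity analysis, so that robustness to skew can be judged without changing the primary estimand.

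The cost is a few sentences, some computing time for permutation across regions and features, and slightly wider intervals with robust standard errors. Sample size and data collection are unchanged.
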